## **Immunizations**

### ***Immunization schedule***

While DNA immunizations will be performed at weeks 0, 4 and 12. 1st MVA will be given at weeks 36 and the 2nd MVA will be given at week 80. The immunization schedule is summarized below:

| Weeks                | -4-8 | -2-4 | 0    | 2 | 4    | 6 | 8 | 12   | 14 | 16 | 36    | 38 | 40 | 44 | 60 | 64     | 76 | 78 | 80    | 82 | 84 | 88 | 104 | 106    |
|----------------------|------|------|------|---|------|---|---|------|----|----|-------|----|----|----|----|--------|----|----|-------|----|----|----|-----|--------|
| Visits               | 1    | 2    | 3    | 4 | 5    | 6 | 7 | 8    | 9  | 10 | 11    | 12 | 13 | 14 | 15 | 16     | 17 | 18 | 19    | 20 | 21 | 22 | 23  | 24     |
| Type of immunization |      |      | DNA1 |   | DNA2 |   |   | DNA3 |    |    | MVA 1 |    |    |    |    | EXIT 1 |    |    | MVA 2 |    |    |    |     | EXIT 2 |

| Arm         | Volunteers | DNA immunization                  | MVA boost               |
|-------------|------------|-----------------------------------|-------------------------|
| I    | 20         | DNA intramuscularly by Bioject    | MVA 10  i.m |
| II   | 20         | DNA id by Bioject                 | MVA 10  i.m |
| IIIa | 10         | Saline intramuscularly by Bioject | Saline i.m              |
| IIIb | 10         | Saline id by Bioject              | Saline i.m              |

## Doses

| Vaccine and delivery method | Route           | Ampoule 1 (env), Left arm               | Ampoule 2 (gag, Rtmult), Right arm      |
|-----------------------------|-----------------|-----------------------------------------|-----------------------------------------|
| DNA by Biojector            | Intramuscularly | 1.0 ml (tot 2.0 mg DNA)                 | 0.9 ml (tot 1.8 mg DNA)                 |
| DNA by Biojector            | Intradermally   | 3 injections of 100ul (Total 0.6mg DNA) | 2 injections of 100ul (total 0.4mg DNA) |

## Mode of Vaccine Delivery

All DNA immunizations will be performed with the Bioject device according to the manufacturer's instruction. Intramuscular injections will be given in the deltoid muscle. Ampoule 1 will be given in the left arm and ampoule 2 in the right arm. During the procedure the overlying skin will be stretched flat prior to applying the Bioject device. To ensure that the fluid reaches the muscle, and that the product does not leak into the surrounding tissues, a decision about the orifice size required will be made individually for each participant, based on published recommendations [29, 30]. Intradermal injections will be given in the skin over the deltoid muscle with the extension supplied by the manufacturer for this purpose. Ampoule 1 will be given in the left arm and ampoule 2 in the right arm. Ten minutes after immunisation, the site will be inspected and any local reactions recorded on the case record form. The MVA-boost injection will be delivered intramuscularly in the deltoid muscle.

The immunisations will take place in an outpatient setting. Participants will be closely observed for 30 minutes after each immunisation, at which point vital signs (pulse, blood pressure and respiratory rate) will be recorded on the case record form, as will any local or systemic reaction. The needles, syringes and other materials will be disposed of according to MNH biohazard regulations. As with any parenteral vaccine, epinephrine and corticosteroids will be available for immediate use should an immediate hypersensitivity reaction, such as anaphylaxis, occur. Intravenous injections of vaccines will NOT be performed. Study vaccine will not be administered to individuals with hypersensitivity to any component of the vaccine. All immediate hypersensitivity reactions will be managed according to the developed SOP's. Volunteers will also be contacted 1-3 days at the clinic following injection for a brief adverse reaction interview. In addition, volunteers will complete diaries over events for 7 days following each vaccination.

### **Safety follow-up in the days following immunization**

A diary card will be given, with instructions and a full verbal explanation, for volunteers to record local and systemic adverse events following immunization, as well as medication taken. Volunteers will be observed on the day of immunization as above, and contacted within 3 days following injection for a brief adverse reaction interview at the clinic. In addition, volunteers will complete diaries over events for 7 days following each vaccination. Contact will be maintained by the clinical team, using a method chosen by the volunteer, as indicated by the evolution of adverse events, up to resolution of solicited local and systemic events. Additional visits may be recommended at the discretion of the clinical and principal investigators, if clinically indicated or in order to clarify observations. All concomitant medication must be recorded in study form CRF 9 (*Appendix xiii*) with the reason for administration, the dosage regimen, the onset and end of treatment.

The following medications are prohibited while the volunteer is in the study:

- Immunomodulatory agents (i.e. immunoglobulin)
- Immunosuppressive agents (i.e., systemic steroids, chemotherapy)
- Live, attenuated vaccines. Other vaccines (subunit or killed) should be given at least two weeks before or two weeks after HIV immunization.

### **Final visit**

Assessments will be undertaken according to schedules as depicted above.

### **Unscheduled visits**

If the volunteer attends or contacts the clinic for any health related changes or event following immunization, a CRF 12 will be filled in, and where appropriate, an adverse event form (CRF 8-1 and CRF 8-II) will be filled in.

### **REIMBURSEMENT**

Regular payments will be made to all volunteers to cover their travel expenses (TShs 5,000.00 x 2) as well as time and inconvenience (TSh 10,000.00) compensation. This will amount to 20,000.00 T.Shs (approx=17.00 USD) per visit. During the study, volunteers will receive hypoallergenic latex condoms free of charge. If any medication is required as a result of the study, this will also be provided free of charge. Such medication will include painkillers, antipyretics and the like. In case of hospitalization/or if further care will be required, these will be covered under the medical insurance; all these will be confined to the period of the study.

#### **IN THE EVENT OF DISCONTINUATION**

Study volunteer may withdraw his/her consent to participate in the study at any time without prejudice. Wherever possible, the tests and evaluations listed for the termination visit will be carried out if the volunteer refuses follow-up according to the protocol visit schedule. The Data and Safety Monitoring Board (DSMB) will be notified of all study withdrawals within 24 hours. Volunteers who withdraw from the study will be replaced only as long as the study is still open for enrolment. No replacement will be allowed when the enrolment is closed. All volunteers who receive at least one immunization will be included in the safety analysis. If a volunteer does not complete the immunization schedule secondary to a serious adverse event or toxicity, he or she will continue to be followed according to the protocol visit schedule, *and, at a minimum*, until the adverse event/toxicity is resolved and/or the cause is identified.

A genuine effort will be made to determine the reason(s) why a volunteer fails to return for the necessary visits. This information will be recorded on the appropriate source document, exit Form CRF 11.

#### **Pregnancy reporting and follow up**

For volunteers who become pregnant before completing the vaccine series, no further immunizations will be given. A positive UPT test result will be communicated to the volunteer and her ineligibility to continue with the study. A pregnancy report form CRF 10, the exit form CRF 11 and an adverse event CRF 8-II are filled in. The volunteer will be followed for all the remaining scheduled visits according to the schedule of procedures for safety evaluation, as well as her antenatal clinic for the maternal outcomes during pregnancy, labor, delivery, and post-delivery periods. The infant outcome will also be sought.

## THE VACCINE (TRIAL PRODUCTS)

### DNA Priming

Will be effected with DNA plasmids derived from puC8 with a kanamycin resistance gene, hCMV promotor, HPV 16 poly A and origin of replication for *E. coli*. They will be carrying HIV-1 genes of subtypes A, B and C. These are pKCMVgp160A, KCMVgp160B, pKCMVgp160C, pKCMVrev, pKCMVp37A(ba), pKCMVp37B, and pKCMVpRTB.

#### *Supply, storage and composition of DNA*

Vecura company (Karolinska University Hospital at Huddinge, Stockholm, Sweden) will be responsible for bulk manufacture of the DNA vaccine, release testing and technical release of vialled product and labelling. All procedures will be according to Good Manufacturing Practice. The presentation is in liquid form, with an extractable volume of 1.0 ml and 2ml vials, which should be stored at  $-20^{\circ}\text{C}$  until use. Care will be taken not to break the cold chain

The DNA plasmids were approved for human use on November 27th 2004 by the Swedish Medical Products Agency, (läkemedelsverket), and the second revision of the protocol ethically cleared by the Swedish Internal Review board, (Regionala forskningsetiska kommittén) December 2004, and will need to have a further approval by the Tanzania Food and Drugs Authority (TFDA)

#### *Labels*

DNA will be packed by Vecura. The trial products will be in vials pre-labelled according to standardised operating procedures. Each vial will be packed in a box labelled with the name of the clinical site and principal investigator, the storage details and the name of the supplier for the product. Cartons will be supplied to the designated pharmacist at MNH for storing the used vials, labelled with the supplier, the name of the trial and protocol version; the volunteer study number; and the name of the clinical site and principal investigator.

Having been manufactured by Vecura Company, the DNA vaccine will be supplied to the study by the Swedish Institute for Infectious Disease Control, 171 82 Solna. SWEDEN.

Prior to use the vials will be thawed at room temperature. When completely thawed the vials will be gently swirled. Care will be taken not to shake or invert the vials.

### MVA Boosting

Boosting will be effected by a Modified Vaccinia Ankara vaccine (MVA-CMDR). The MVA - CMDR, produced by WRAIR/NIH, is a live recombinant poxvirus vector vaccine that has been genetically engineered to express the following HIV-1 genes:

1. **gp160** (Subtype E, CM235), and
2. **gag** and **pol** (integrase-deleted and reverse transcriptase nonfunctional, Subtype A, CM240).

MVA-CMDR is formulated in a liquid form in vials and will be administered at a dose of  $10^8$  pfu by intramuscular route following appropriate dilutions.

#### *Supply, storage and composition of MVA*

Walter Reed Army Institute of Research (WRAIR), USA, will be responsible for the bulk manufacture of the clinical material, release testing, as well as the technical release of vialled product, and labeling. The full address of the manufacturer for the MVA-DNA used for the 1st boost is: Walter Reed Army Institute of Research (WRAIR), [name], Department of Biologics Research The Pilot Bioproduction Facility, [name] 20910, USA The MVA-DNA to be used for the 2nd boost is produced by Advanced Biosciences Laboratories, Inc. [name], USA using the same seed lot as for the 1st boost All procedures will be according to Good Manufacturing Practice. The presentation is in liquid form, with an extractable volume of 1ml vials, which should be stored at -20 °C until use. Care should be taken not to break the cold chain. The product has already received approval from the USA Food and Drugs Authority (FDA), and the Swedish Medical Products Agency and will be presented to the TFDA for approval before use in Tanzania.

#### **Dispensing records and disposal of unused product**

The designated pharmacist will, upon receipt of supplies prior to commencement of the trial, conduct an inventory and complete a receipt, one copy of which will be retained at the site, and the original returned to the supplier (Karolinska Institute, Sweden). During the trial the pharmacist will be responsible for reviewing the dispensing log. On the day of immunization the study nurse will fill in the request form with the study number, date of birth, and immunization number. Upon receipt of the syringes with the vaccine from the pharmacist, the study nurse will deliver the vaccine. The immunization number and date will be entered against the study number in the dispensing log. The vial label will be cross-checked against the details on the prescription and dispensing log by two individuals (pharmacist and nurse), prior to the vaccine/placebo being administered.

The Pharmacist will be responsible for ensuring that the return of used vials is recorded in the dispensing log at the end of the clinical session, and that they are placed in the appropriate volunteer carton. At the end of the trial all used and unused vials will be checked against the inventory by the monitor before disposal on site according to MNH biohazard regulations. Documentation of disposal will be provided to the monitor and supplier. During the trial, product accountability will be monitored by the prescriptions, the dispensing log, the returns, the trial register and data collected on the clinical research forms.

## END POINTS

### Primary

#### *Safety*

The safety of immunization with the seven DNA plasmids carrying HIV-1 genes will be assessed by *clinical features as well as standard biochemical and haematological laboratory tests*. Any worsening of the severity grade will be considered for causality with the vaccine.

The alternative routes of immunization (intramuscularly and intradermally with the Bioject device) will be evaluated by assessing local (pain, cutaneous reactions including induration), general (fever, chills, headache, nausea, vomiting, malaise, myalgia) and other unsolicited adverse events on vaccination day and within 7 days. Any grade 3 or 4 event will be taken as an indication that the arm is less tolerable.

The primary safety parameters will be graded according to *appendix xiv*, and are:

1. Local adverse event Grade 3 or above (pain, cutaneous reactions including induration)
2. Systemic adverse event Grade 3 or above (temperature, chills, headache, nausea, vomiting, malaise, and myalgia)
3. Other clinical or laboratory adverse event Grade 3 or above confirmed at examination or on repeat testing respectively

Tests for possible toxicity due to vaccination will include: Liver function tests, renal function tests and full blood picture. Any event attributable to vaccine leading to discontinuation of the immunization regimen must be documented.

Data on local and systemic events listed above will be solicited with specific questions or using a diary card for a minimum of 7 days following each immunization. Data on other clinical events and laboratory events will be collected with an open question at each visit and through routine scheduled investigations respectively.

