#### Study Design

Randomised, controlled, double blinded study. The laboratory staff will also be blinded to the immunization regimens.

| Arm  | Volunteers | DNA immunization                     | MVA boost                               |
|------|------------|--------------------------------------|-----------------------------------------|
| I    | 20         | DNA 3.8mg intramuscularly by Bioject | MVA 10  pfu intramuscularly |
| II   | 20         | DNA 1.0mg intradermally by Bioject   | MVA 10  pfu intramuscularly |
| IIIa | 10         | Saline intramuscularly by Bioject    | Saline i.m                              |
| IIIb | 10         | Saline id by Bioject                 | Saline i.m                              |

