#### **Endpoints**

##### ***Primary***

The safety of immunization will be assessed by clinical features and standard biochemical and haematological laboratory tests. Adverse events will be evaluated by assessing local (pain, cutaneous reactions including induration), general (fever, chills, headache, nausea, vomiting, malaise, myalgia) and other unsolicited adverse events

within 7 days of vaccination as possibly or probably related to the immunization. Any grade 3 or 4 event will be taken as an indication that the vaccination arm is less tolerable. The magnitude and quality of humoral (neutralizing and binding antibodies) as well as cellular immune responses as elicited by the different schedules of immunization will be determined to assess immunogenicity.

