### **STATISTICAL CONSIDERATIONS**

By the end of this study 60 volunteers will have been exposed to DNA or placebo as well as MVA or saline placebo and described in the quantitative and qualitative immunogenicity and safety evaluation.

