### **Safety data**

The number and percentage of subjects experiencing any adverse events (AE), grade 3 or 4 adverse events, serious adverse events (SAE), and the number of events reported, will be summarized by severity and reported relationship to study treatment for each treatment group, both for all adverse events and by type of adverse event. Calculation of incidence rates of adverse events will include each subject only once, either according to worst severity or first reported event.

Rates of the various adverse events will be compared between the study arms using Fisher's exact test. Rates will be summarized using exact binomial confidence intervals

Safety haematological and biochemical laboratory parameters will be summarized at each study visit according to study arm. Comparisons will be done using 2-sample t-tests or non-parametric equivalents as appropriate to the data

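### The rule that any grade 3 or 4 event marks an arm as less tolerable sets no count, difference or explicit reference arm, and can diverge from the planned Fisher comparison with no precedence stated.

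*Protocol*

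**What the plan says.** The Safety part of the protocol's END POINTS section introduces the comparison: "The alternative routes of immunization (intramuscularly and intradermally with the Bioject device) will be evaluated by assessing local", followed by the general and unsolicited events, on the vaccination day and within 7 days. The next sentence is the rule: "Any grade 3 or 4 event will be taken as an indication that the arm is less tolerable". The list of primary end-points under STATISTICAL CONSIDERATIONS repeats both sentences in substance. The synopsis (Endpoints, Primary) carries the rule too, but refers to the vaccination arm and follows a sentence on events "within 7 days of vaccination as possibly or probably related to the immunization".

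Neither END POINTS nor STATISTICAL CONSIDERATIONS attaches a relatedness condition to the rule. The adverse event definition under SAFETY ASSESSMENTS counts events regardless of relation to vaccine, including intercurrent illness and injury.

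The Safety data section plans number and percentage of subjects with grade 3 or 4 events, by severity and relationship, each subject counted once. It then states: "Rates of the various adverse events will be compared between the study arms using Fisher's exact test", and "Rates will be summarized using exact binomial confidence intervals". No significance level or sidedness is given.

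The two active arms have 20 volunteers each ("DNA 3.8mg intramuscularly by Bioject" and "DNA 1.0mg intradermally by Bioject"), and the two saline groups have 10 each.

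**The concern.** Less tolerable is a comparative statement, but the rule depends only on whether an arm has had at least one event. It does not look at the other arm. With 20 volunteers per arm a single event can easily fall in one arm and not the other by chance. When events are common, both arms carry the label and the rule cannot rank them.

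The protocol therefore holds two criteria for the same primary safety data, the one-event label and the between-arm analysis, and does not say which one supports the tolerability conclusion. If the label were reported as the finding, one route could be described as less tolerable than the other on data that the planned analysis treats as uninformative. The difference in relatedness wording adds a second ambiguity: whether an unrelated illness in the 7 days after an injection triggers the label depends on which section is followed.

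**Working it through.** The protocol states no error rate or power for this rule, so there is no figure of its own to reproduce.

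**Inputs.** Arms I and II, n = 20 each (Study Design table). Trigger: at least one grade 3 or 4 event in the arm. Let p be the true chance that a volunteer has at least one such event in the counted windows, the same in both arms. The protocol gives no p, so a range is shown. Fisher's test is taken as two-sided at 0.05, an assumption.

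**Chance labelling of equal arms.**
- Arm labelled: a = 1 − (1 − p)^20
- Exactly one arm labelled: 2a(1 − a)
- Both labelled: a²
- Fisher column: full enumeration of all 21 × 21 outcomes under the same p

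Example, p = 1%: a = 1 − 0.99^20 = 0.182; 2 × 0.182 × 0.818 = 0.298.

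| p | One given arm labelled | Exactly one labelled | Both labelled | Fisher separates |
|---|---|---|---|---|
| 0.1% | 2.0% | 3.9% | <0.1% | <0.01% |
| 1% | 18.2% | 29.8% | 3.3% | <0.01% |
| 2% | 33.2% | 44.4% | 11.0% | 0.005% |
| 5% | 64.2% | 46.0% | 41.2% | 0.19% |
| 10% | 87.8% | 21.4% | 77.2% | 1.2% |
| 20% | 98.8% | 2.3% | 97.7% | 2.3% |

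The exactly-one probability peaks at 50% near p = 3.4%. It is at least 20% for p from about 0.6% to 10.3%, and under 10% for p below about 0.3% or above about 14%.

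**Divergence from Fisher, 20 v 20.**
- 1/20 v 0/20: the rule labels one arm. With one event in total, the two possible tables each have probability 1/2, so p = 1.00. Exact 95% intervals: 0.1% to 24.9% for 1/20, and 0% to 16.8% for 0/20.
- 4/20 v 0/20: 2 × C(20,4)/C(40,4) = 2 × 4,845/91,390 = 0.106.
- 5/20 v 0/20: 2 × C(20,5)/C(40,5) = 2 × 15,504/658,008 = 0.047. This is the smallest split against zero that reaches 0.05.
- 1/20 v 7/20: the rule labels both arms alike. 2 × [20 × C(20,7) + C(20,8)]/C(40,8) = 2 × (1,550,400 + 125,970)/76,904,685 = 0.044.

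The two criteria can thus part in either direction.

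**What zero events excludes.** Upper exact 95% limit for 0/20: 1 − 0.025^(1/20) = 16.8%.

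**The case against.** The strongest reply is that the rule is only an indication, and that the Safety data section is a conventional analysis which nothing says the rule replaces. Much of this stands, and it limits what can be claimed.

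- A reader might infer that the rule selects or rejects a regimen. The protocol does not support that: no section ties the label to choosing a route, closing an arm or any later decision, and withdrawal and study stopping have their own criteria.
- A reader might infer an outright contradiction with Fisher's test. That is too strong. A descriptive flag can sit beside a non-significant test, and p=1.00 on 1/20 v 0/20 does not show equal tolerability. What remains is that the two can diverge and no precedence is stated.
- A reader might say that there is no comparator at all. The preceding sentence implies i.m. versus i.d.; what is missing is an explicit reference in the rule. Labelling of a saline group is likewise less clear than END POINTS alone suggests, since the synopsis speaks of the vaccination arm.
- A reader might say that two sections define the rule on any-cause events. They are silent on relatedness, and both say that worsening grades are considered for causality. This is an inconsistency with the synopsis, not a stated any-cause rule.
- The size depends on an event rate that the protocol does not give. At very low or high rates chance separation is small, so no unconditional statement that it happens often is justified.

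A SAP that is not at hand might settle precedence. The sentence is nevertheless fixed in the protocol in three places, and a SAP would have to override it.

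**Conclusion.** The point holds as a defect of wording with a real effect on how a primary safety endpoint is read. Taken as written, the rule attaches a comparative label to an arm on one event. For a shared per-volunteer rate between about 0.6% and 10.3% it would separate two equally tolerable arms of 20 in 20% to 50% of trials. At 10% it would label both in 77% of trials and so fail to rank them. These figures assume equal true rates and independent volunteers; the event rates, and the two-sided 0.05 level for Fisher's test, are assumptions because the protocol gives none. The divergent examples (1/20 v 0/20 and 1/20 v 7/20) do not depend on any assumed event rate. The conclusion does not extend to a claim that a regimen would be chosen or dropped on this label.

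**What to change.** 1. In the synopsis, END POINTS and STATISTICAL CONSIDERATIONS, delete the sentence, or label it a descriptive flag that carries no between-arm conclusion.
2. State that relative tolerability of the two routes is judged from the Safety data comparison: the proportion of volunteers with at least one grade 3 or 4 event, by arm, with the between-arm difference and exact intervals. Proportions, exact intervals and Fisher's test are already planned there; the difference and the statement of precedence are the additions.
3. Reconcile the relatedness wording across the three places, for example by reporting both any-cause and possibly or probably related events. Showing both is useful because the study nurse is told whether the assignment is ID or IM (second screening visit), so relatedness cannot be judged blind to route.
4. State what zero events can exclude: an upper exact 95% limit of 16.8% for 0/20.

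The safety-review and stopping provisions are not touched by this change. Pooling the active arms against the saline groups (40 v 20) for the MVA injections is an option, not a requirement; it assumes that the DNA route does not affect reactions to MVA.

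The cost is protocol wording and a small addition to a planned table. The downside is that the tolerability conclusion becomes an interval, and at 20 per arm a wide one, instead of a yes/no label.

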#### **Local adverse events**

Pain in the muscle injected will be graded by the volunteer according to the criteria in the specific appendix as mild (1) moderate (2), severe (3) or serious (4) and recorded in the appropriate case record form or once the volunteer has left clinic, in the diary card. Redness and or induration will be recorded as the maximum diameter and expressed as a proportion of the arm circumference and graded on this criteria and the presence of symptoms according to the specific appendix. Arm circumference will be measured at screening, at the point one third of the way down from the acromio-clavicular joint towards the elbow joint in the injected arm. Investigating personnel will record the maximum diameter, as well as the presence of any itching or other discomfort and any medication taken for relief of symptoms. Blistering (vesiculation) or ulceration will be graded according to size, depth, time to healing and character of blisters (blood-filled).

The sole presence of an induration following intramuscular injection considered grade 3 will not be sufficient to stop the trial (see table). Clinical staff will complete the case record form following each immunisation. In the event that there are two observations on the same day, those confirmed at a visit will take precedence over diary card observations in the analysis. Study personnel should verify all grade 3 or 4 events.

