#### *The primary end-points are:*

1. The safety of immunization with the seven DNA plasmids carrying HIV-1 genes as assessed by clinical signs, and standard biochemical/haematological laboratory tests where any worsening of the severity grade will be considered for causality by the vaccine

2. A qualitative and quantitative evaluation of the magnitude and quality of humoral (neutralizing and binding antibodies, by serology) as well as cellular (cytotoxic T-cell, IFN-gamma by ELISPOT, T-cell proliferation (Fascia) and intracellular cytokines by flow cytometry) immune responses as elicited by the different schedules of immunization

The alternative routes of immunization (im and id with the Bioject device) will be evaluated for adverse events by assessing local (pain, cutaneous including induration), general (fever, chills, headache, nausea, vomiting, malaise, myalgia) and other unsolicited adverse events within 7 days. Any grade 3 or 4 event will be taken as an indication that the arm is less tolerable

*The secondary endpoints are:*

1. A qualitative and quantitative assessment on the presence of necessary infrastructure and human capacity to conduct HIV-related vaccine studies at MUHAS.

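### Graded reaction severity is collected and tabulated but never compared between the i.m. and i.d. routes; a pre-specified rank test on worst grade, added to the planned Fisher tests, would use it at almost no cost

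*Protocol*

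**What the plan says.** In the Protocol, End points, Primary, Safety, the i.m. and i.d. routes are to be evaluated by local, general and unsolicited events. Two of the three primary safety parameters there are "Local adverse event Grade 3 or above (pain, cutaneous reactions including induration") and "Systemic adverse event Grade 3 or above (temperature, chills, headache, nausea, vomiting, malaise, and myalgia"). The same section gives a reading rule: "Any grade 3 or 4 event will be taken as an indication that the arm is less tolerable". The list of primary end-points under Statistical considerations repeats the purpose: "The alternative routes of immunization (im and id with the Bioject device) will be evaluated for adverse events by assessing local" and general reactions.

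The data collected are finer than the cut. Under Local adverse events, pain is graded 1 to 4 by the volunteer, and "Redness and or induration will be recorded as the maximum diameter and expressed as a proportion of the arm circumference". Under Systemic adverse events, each symptom is graded daily for 7 days or until it resolves.

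Under Statistical considerations, Safety data, the plan counts any adverse event, grade 3 or 4 events and serious events, and summarises them by severity. It then states: "Rates of the various adverse events will be compared between the study arms using Fisher's exact test". In that section t-tests or non-parametric equivalents are named only for laboratory values. The Immunogenicity Data section names them for continuous immunogenicity endpoints. No ordinal or continuous comparison is named for reactions.

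**The concern.** Comparing the routes for tolerability is part of the primary safety endpoint. Each yes/no cut keeps one boundary of the severity scale and drops the others. Grade 3 or above ignores all movement among grades 0, 1 and 2, which is where most volunteers may be expected to fall: the background section on the ongoing trial describes the vaccines as very safe so far. Any grade ignores movement above grade 1. A route that shifts reactions upward by one step across the scale could show in the severity table and still face no formal comparison built to detect it, although the protocol has already collected what that comparison needs.

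**Working it through.** **Inputs from the protocol.** The Study Design table gives 20 volunteers in Arm I ("DNA 3.8mg intramuscularly by Bioject") and 20 in Arm II (DNA intradermally). It also gives the arms different DNA amounts, so the contrast is between two regimens and not route alone. No significance level, power, effect size or grade rates are given for safety, so there is no planned figure to reproduce.

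**Assumptions.** Two-sided 5%; one worst grade per volunteer; three profiles for the milder arm (grades 0/1/2/3): A 50/35/13/2%, B 25/50/22/3%, C 15/45/35/5%; the other arm shifted by a common odds ratio (OR) of 3 or 4.

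**Step 1: what Fisher needs.** For 0 of 20 against 5 of 20, p = 2 × C(20,5)/C(40,5) = 2 × 15504/658008 = 0.047. For 0 against 4, p = 2 × 4845/91390 = 0.106. With one event in the milder arm, 1 against 6 gives 0.091 and 1 against 7 gives 0.044.

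**Step 2: the shift.** At each cut, odds in the other arm = OR × odds in the milder arm. For profile A with OR 4:
- any grade: 0.50/0.50 × 4 = 4, so 80%
- grade 2 or above: 0.15/0.85 × 4 = 0.706, so 41.4%
- grade 3 or above: 0.02/0.98 × 4 = 0.0816, so 7.5%

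**Step 3: power.** Fisher power is exact: the sum over Binomial(20, p1) × Binomial(20, p2) of outcomes with p ≤ 0.05. Rank-test power is simulated (1,500 trials per case, 999 permutations each).

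| Profile, OR | Fisher ≥3 | Fisher any | Fisher ≥2 | Rank test | Gain over best cut |
|---|---|---|---|---|---|
| A, 4 | 1% | 41% | 35% | 61% | 20 |
| B, 4 | 3% | 20% | 42% | 62% | 20 |
| C, 4 | 11% | 8% | 42% | 62% | 19 |
| A, 3 | 0% | 27% | 20% | 44% | 17 |
| B, 3 | 1% | 14% | 27% | 40% | 13 |
| C, 3 | 5% | 6% | 27% | 42% | 16 |

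Simulation error is about ±2.5 points (1.96 × √(0.6 × 0.4/1500)). Type I error of the rank test was 4.5 to 4.7%. Using the large-sample p-value in place of the exact one gives about 43 to 63% power and a gain of about 15 to 22 points.

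**Step 4: where the rank test loses.** Start from profile B and raise only grade 3. At 3% to 15% the two tests are about equal (Fisher ≥3 10%, rank 9%). At 3% to 30% Fisher ≥3 has 56%, against about 29 to 34% for the rank test, depending on which lower grades the extra severe cases are drawn from.

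**The case against.** Several counter-arguments have force.

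- **Fisher is not confined to grade 3.** A reader might infer that the whole route comparison has almost no power. The documents do not support that. The Safety data section also counts any adverse event and compares the various events, so an any-grade comparison is within the plan, with up to 41% power in these examples. Severity is tabulated too. The near-zero figures belong to the grade 3 parameters alone.
- **Tolerability is not read by significance.** A reader might fear that a non-significant Fisher result will be taken as equal tolerability. The stated rule instead marks an arm on any grade 3 or 4 event. Its weakness is the opposite one. If both arms have a true 5% rate, P(at least one event) = 1 − 0.95^20 = 0.64, and exactly one arm is flagged with probability 2 × 0.64 × 0.36 = 0.46.
- **The gain is moderate.** Set against the grade 3 cut alone, or against only the grade 3 and any-grade cuts, it looks much larger. Once a grade 2 cut is included it is about 13 to 22 points. The protocol does not name a grade 2 comparison, however, and choosing the best cut after seeing the data would not be a valid test.
- **Grade 3 is a proper safety-signal threshold** in a 60-person trial that claims no power, and a rank test with 40 to 63% power can still miss a real shift.
- **Diameter is not directly comparable.** Per the Doses table, i.d. volunteers have five injection sites (3 + 2) and i.m. volunteers two, so a maximum is taken over unequal numbers of sites. Grading also uses symptoms.
- **An analysis plan, not shown, may add an ordinal test.** That is possible, but the protocol itself fixes the grade 3 cut and names the test, and those can be assessed as written.

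These points limit the claim. They do not give a reason to leave the ordered grades uncompared.

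**Conclusion.** The point holds as a moderate, inexpensive improvement. As written, no between-arm comparison of reactions uses the ordered severity grade. Under proportional-odds shifts of 3 to 4, a rank test on worst grade has about 40 to 63% power, against about 0 to 11% for Fisher at grade 3 or above, 6 to 41% for any grade and 20 to 42% for grade 2 or above. These figures rest on assumed profiles, an assumed two-sided 5% level and a shift across the whole scale. When only severe reactions rise, Fisher at grade 3 or above equals or beats the rank test. The rank test therefore belongs beside the planned analyses and should not replace them.

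**What to change.** In Statistical considerations, Safety data:

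1. Keep the grade 3 or above and any-grade counts, with exact intervals and Fisher tests.
2. Add, as the pre-specified i.m. versus i.d. reactogenicity comparison, an exact Wilcoxon rank-sum test on each volunteer's worst solicited grade over the DNA injections, with no reaction counted as 0. Run it once for local and once for systemic reactions.
3. Report maximum redness or induration descriptively. If it is compared, state the unequal number of injection sites (five i.d., two i.m.) with the result.

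The cost is a few sentences and a few lines of code, with no new data, visits or volunteers. The downsides are two extra tests to interpret and lower sensitivity than grade 3 or above when a route raises only the most severe reactions, which is why item 1 stays.
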